# A Personalized Physical Activity Program With Activity Trackers and a Mobile Phone App for Patients With Metastatic Breast Cancer: Protocol for a Single-Arm Feasibility Trial

**DOI:** 10.2196/10487

**Published:** 2018-08-30

**Keywords:** metastatic breast cancer, physical activity, oxidative stress, activity trackers, feasibility

## Abstract

**Background:**

About 5% of breast cancer cases are metastatic at diagnosis, and 20%-30% of localized breast cancer cases become secondarily metastatic. Patients frequently report many detrimental symptoms related to metastasis and treatments. The physical, biological, psychological, and clinical benefits of physical activity during treatment in patients with localized breast cancer have been demonstrated; however, limited literature exists regarding physical activity and physical activity behavior change in patients with metastatic breast cancer.

**Objective:**

The primary objective of this study is to assess the feasibility of a 6-month physical activity intervention with activity trackers in patients with metastatic breast cancer (the Advanced stage Breast cancer and Lifestyle Exercise, ABLE Trial). Secondary objectives are to examine the effects of physical activity on physical, psychological, anthropometrics, clinical, and biological parameters.

**Methods:**

We plan to conduct a single-center, single-arm trial with 60 patients who are newly diagnosed with metastatic breast cancer. Patients will receive an unsupervised and personalized 6-month physical activity program that includes an activity tracker Nokia Go and is based on the physical activity recommendation. Patients will be encouraged to accumulate at least 150 minutes per week of moderate-to-vigorous intensity physical activity. Baseline and 6-month assessments will include anthropometric measures, functional tests (eg, 6-minute walk test and upper and lower limb strength), blood draws, patient-reported surveys (eg, quality of life and fatigue), and clinical markers of tumor progression (eg, Response Evaluation Criteria In Solid Tumors criteria).

**Results:**

Data collection occurred between October 2016 and January 2018, and the results are expected in August 2018.

**Conclusions:**

The ABLE Trial will be the first study to assess the feasibility and effectiveness of an unsupervised and personalized physical activity intervention performed under real-life conditions with activity trackers in patients with metastatic breast cancer.

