Reportedly, regular physical activity and fatigue can affect blood biomarker levels, including inflammatory markers [26] and oxidative stress [27]. Evidence from randomized controlled trials (RCTs) has indicated an effect of physical activity in patients with cancer on the levels of circulating growth factors and cytokines (eg, interleukin 6 and tumor necrosis factor alpha) [28,29] and suggests that physical activity might markedly alter the frequency and functional competence of immune cell subsets of the innate immune system (eg, neutrophils, monocytes, and natural killer cells) [30,31]. Concerning the oxidative stress, an excessive accumulation of oxidative stress in cells has been shown to induce marked cellular and molecular damages and likely plays an important role in carcinogenesis, tumor promotion, and breast cancer recurrence and metastasis [32-34]. Moreover, plasma antioxidant defenses seem to be lower in women with breast cancer [34]. On the contrary, physical activity programs have shown to decrease the oxidative stress in patients with chronic diseases other than cancer, in particular through the improvement of enzymatic antioxidant defenses [27,35].

The Advanced stage Breast cancer and Lifestyle Exercise (ABLE) Trial was designed to address the gaps in the current literature. The primary aim is to determine the feasibility of an unsupervised and personalized physical activity intervention in patients with metastatic breast cancer. The secondary aims are to investigate (1) how the physical activity intervention changes the total global physical activity, sedentary time, and physical fitness; (2) how the physical activity intervention changes patient-reported outcomes, including the quality of life and fatigue; (3) how the physical activity intervention changes patients’ anthropometric measurements and body composition; (4) the barriers and facilitators of the adherence to a physical activity program; and (5) whether the physical activity intervention affects the oxidative stress and inflammation as biomarkers of the tumor progression.

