### Study Population

The inclusion criteria for this study are as follows: (1) female; (2) aged 18-78 years; (3) newly diagnosed with primary or secondary metastatic breast cancer histologically confirmed (ie, within the last 3 months) and treated in a cancer center by chemotherapy or radiotherapy or hormonal therapy or targeted therapy; (4) Eastern Cooperative Oncology Group Performance status <2; (5) able to speak and understand French and able to complete questionnaires and follow instructions in French; and (6) valid health insurance affiliation. For patients willing to participate in the study, confirmation from their treating oncologist of no contraindications to physical activity is required.

The exclusion criteria for this study are as follows: untreated brain metastases; pregnancy; and contraindications to physical activity (eg, uncontrolled hypertension, cardiac disease). All patients must sign an informed consent form.

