### Statistical Analysis

#### Sample Size

The sample size was defined empirically to explore the feasibility of the program according to the enrollment potential in the study center. Because the main objective of the ABLE Trial was to assess the feasibility of a physical activity intervention in women with metastatic breast cancer, without major regard for the efficiency, no formal calculation was performed. Given that 200 patients are treated annually for metastatic breast cancer in the Center Léon Bérard and that 60% of patients are expected to survive for at least 6 months, with a projected acceptance rate of 50%, the pilot study will aim to recruit 60 patients within 9 months.

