#### Statistical Methods

Patients’ characteristics will be described at D1 and M6 using the mean and SD for quantitative data, frequency, and percentage for qualitative data.

The primary outcome to assess the feasibility of the study will be the proportion of patients achieving the physical activity recommendations corresponding to 150 minutes per week of moderate physical activity evaluated by the IPAQ score during the last week of the study. In addition, we will estimate the proportion of patients who agreed to participate in the ABLE Trial among eligible patients. The reasons for refusal will be documented and described as well.

The secondary outcomes to assess will be the evolution of physical activity, anthropometric, physical fitness, psychological, and biological variables between the initiation (D1) and the completion (M6) of the physical activity intervention using Wilcoxon signed-rank tests. In addition, the level of physical activity according to biological, psychological, and clinical outcomes adjusted on potential confounders, including age, treatment, and number of visits, will be explored using multiple linear regressions. Moreover, the level of oxidative stress will be correlated to the RECIST criteria. Data on barriers and facilitators of the adherence to a physical activity program from D1 to M6 will be compared by Mac Nemar tests. All statistical analyses will be performed using SAS software (version 9.4. SAS Institute Inc, Cary, NC, USA).

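### The abstract and aims claim effectiveness and effects on outcomes, which a single-arm before-after comparison in women under treatment for new metastatic disease cannot show

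*Protocol article*

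**What the plan says.** The causal wording appears in three places in the protocol article.

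- Abstract, Conclusions: the trial will be "the first study to assess the feasibility and effectiveness of an unsupervised and personalized physical activity intervention".
- Abstract, Objective: "Secondary objectives are to examine the effects of physical activity on physical, psychological, anthropometrics, clinical, and biological parameters".
- Introduction, last paragraph: aim 2 is "how the physical activity intervention changes patient-reported outcomes, including the quality of life and fatigue", and aims 1 and 3 use the same verb for activity, fitness and body measures. Aim 5 is "whether the physical activity intervention affects the oxidative stress and inflammation as biomarkers of the tumor progression".

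The design is given in the Abstract's Methods: "We plan to conduct a single-center, single-arm trial with 60 patients who are newly diagnosed with metastatic breast cancer". Study Population requires a diagnosis within the last three months and patients "treated in a cancer center by chemotherapy or radiotherapy or hormonal therapy or targeted therapy".

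Under Statistical Analysis, Sample Size explains that no formal calculation was made because feasibility was the aim, "without major regard for the efficiency" (in context, efficacy). Statistical Methods then states: "The secondary outcomes to assess will be the evolution of physical activity, anthropometric, physical fitness, psychological, and biological variables", compared between day 1 (D1) and month 6 (M6) by Wilcoxon signed-rank tests. The same section plans multiple linear regressions adjusted for age, treatment and number of visits, a correlation of oxidative stress with RECIST, and McNemar tests for barriers and facilitators.

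The limitations, in the Discussion under Principal Findings, name the limited sample size and the unvalidated tracker.

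**The concern.** Effectiveness, and the statement that an intervention affects a biomarker, are claims about what would have happened without the intervention. A one-arm trial has no observation of that. The gap matters more here than in a stable population. These women are starting or have just started treatment for metastatic disease, and fatigue, quality of life, weight, blood cell counts and cytokines can all plausibly move over six months because of the treatment or the disease.

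At stake is how the secondary results will be read. With the aims worded as they are, a fall in fatigue or in an oxidative marker between D1 and M6 would answer the stated question as a programme effect. The Discussion says the results will help to design a multicentre randomised trial, so a misattributed change could become its assumed effect.

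**Working it through.** The plan gives no numerical figure on which the effectiveness claim rests, so there is none to reproduce. The check is one of identification, followed by an illustration.

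**1. What the signed-rank test addresses.** Write a patient's change from D1 to M6 as δ + γ + error. Here δ is the programme's effect and γ is everything else acting over the six months (anticancer treatment, disease course, adaptation to the diagnosis). The paired test asks whether δ + γ is centred on zero among patients who have an M6 value. One arm gives one equation in two unknowns. The aims ask about δ; the data give δ + γ. A control group would be needed to estimate γ.

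**2. Whether another planned analysis fills the gap.** The regressions relate activity level to outcomes among women who all received the programme. Adjustment for age, treatment and visits does not create an unexposed comparison, and women who are doing better may be active because they are doing better. The RECIST correlation links two outcomes with each other. The McNemar tests concern barriers and facilitators. None estimates γ.

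**3. Who is analysed.** A paired test needs an M6 value, so patients who die or withdraw before then do not contribute. The article gives no expected loss among those enrolled. Sample Size expects 60% of the centre's patients to survive at least six months, but uses this in the recruitment projection. The number of pairs is therefore an assumption: 60 if nobody is lost, 60 × 0.60 = 36 if the 60% applied to the enrolled patients.

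**4. Illustration with no programme effect (δ = 0).** Assumptions, none of them from the document: normally distributed changes, two-sided 0.05 per test, and γ equal to 0, 0.3 or 0.5 SD of the change. Share of 2,000 simulated trials with p < 0.05 by the signed-rank test:

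| γ (SD of change) | 36 pairs | 60 pairs |
|---|---|---|
| 0 | 5.7% | 4.2% |
| 0.3 | 42.5% | 62.6% |
| 0.5 | 82.6% | 96.2% |

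Normal approximation as a check at γ = 0.3, Φ(γ√n − 1.96):
- 36 pairs: Φ(1.80 − 1.96) = Φ(−0.16) = 0.44
- 60 pairs: Φ(2.32 − 1.96) = Φ(0.36) = 0.64

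Both agree with the simulation. A moderate drift from other causes often gives a significant result, and more patients make this more likely.

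**5. Internal consistency.** Sample Size excuses the absence of a calculation by setting efficacy aside. The Abstract's Conclusions announce effectiveness. The limitations do not reconcile the two.

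**The case against.** The strongest reply is that the exploratory frame is largely present. The title calls this a single-arm feasibility trial, the primary objective is feasibility, Sample Size calls it a pilot, Statistical Methods speaks neutrally of the evolution of variables between D1 and M6, and the Discussion promises preliminary data to inform a randomised trial. This stands as mitigation: it makes the fault one of wording in the secondary claims. It does not retract the word *effectiveness* in the abstract or the causal verbs in the aims, and nothing in the article says that before-after changes are not attributable to the programme.

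Some stronger readings are tempting, but the document does not support them.

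- *That uncorrected signed-rank tests are the only analysis.* Statistical Methods also lists the regressions, the RECIST correlation and the McNemar tests, and promises means and SDs of patients' characteristics at both times.
- *That chance findings among many tests are near certain.* Statistical Methods names families of variables, not a list of tests, and states no alpha. Many of the scores are related, some being parts of one total. Handling of multiplicity may sit in an analysis plan that is not shown.
- *That 40% of enrolled patients will be missing at M6.* The 60% survival figure is part of a recruitment projection, and entry also requires performance status below 2. Selective loss is possible, but its size is unknown.
- *That regression to the mean drives the changes.* Entry sets no threshold on fatigue, quality of life or any biomarker.

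**Conclusion.** The point holds as an overstatement of what the design can show. It reaches the abstract conclusion, the secondary objective and secondary aims 1, 2, 3 and 5; aim 4, on barriers and facilitators, is not affected. The primary feasibility outcome is also unaffected.

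The conclusion rests on stated features alone: one arm, a recent metastatic diagnosis, concurrent treatment, and D1-M6 comparison. The simulated percentages depend on the assumed drift and number of pairs. They illustrate the problem and do not forecast this trial. A reader might infer that the secondary analyses are worthless or that a programme effect has been ruled out; neither follows. The changes remain useful as description and as planning input. The correction should be made, because it alters what the trial may conclude.

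**What to change.** 1. Delete *effectiveness* from the Abstract's Conclusions, leaving feasibility.
2. Reword the secondary objective and aims 1, 2, 3 and 5 as describing change from D1 to M6 during the programme.
3. State in Statistical Methods that secondary results are exploratory and not attributable to the intervention.
4. Add two limitations to the Discussion: there is no control group, and before-after comparisons are restricted to patients with M6 data.

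As a recommendation, report each change as an estimate with a 95% confidence interval, which would serve the planned randomised trial better than a p-value. This may already be in an analysis plan that is not shown.

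The cost is wording and more modest claims. Follow-up was complete in January 2018 according to the Results section, and none of these changes touches the design, the data collected or the primary outcome.

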**Trial Registration:**

ClinicalTrials.gov NCT03148886; https://clinicaltrials.gov/ct2/show/NCT03148886 (Accessed by WebCite at http://www.webcitation.org/71yabi0la)

**Registered Report Identifier:**

RR1-10.2196/10487

## Introduction

Breast cancer is the most common cancer among women worldwide with >1.6 million new cases diagnosed annually and 54,062 incident cases in France in 2015 [1]. About 5% of breast cancer cases are metastatic at diagnosis, and 20%-30% of localized breast cancer cases become secondarily metastatic [2-4]. Metastatic breast cancer is considered incurable, and treatments are proposed to improve the quality of life and overall survival.

Fatigue and reduced quality of life are frequent in patients with metastatic breast cancer related to the site of metastasis and cancer treatment [5,6]. Evidence from meta-analyses and systematic reviews in patients with localized breast cancer has demonstrated the benefits of physical activity on multiple health outcomes [7-12]. However, only five studies have focused on the investigation of physical activity interventions in patients with metastatic breast cancer [13-17] despite the need, desire, and ability of these patients to engage in physical activity [14,15,18]. Some studies have already investigated the association among metastatic cancer, fatigue, and physical activity; however, the results are mixed and warrant confirmation, specifically in patients with metastatic breast cancer [13-16].

In the cancer context, activity trackers with step pedometers are increasingly being used to measure physical activity and promote physical activity behaviors [19-21]. The benefits of mobile eHealth apps and pedometers on physical fitness, physical activity, and quality of life of patients with breast cancer have been reported [22]. These devices might motivate people to remain active and facilitate reaching a personal or recommended goal because of the feedback received in real time (eg, steps) [23-25]. In addition, activity trackers are often linked to a mobile app with a personal interface that provides a summary of the physical activity (ie, light, moderate, and vigorous intensity), sedentary time, and the number of steps accumulated per day, week, and month.

Reportedly, regular physical activity and fatigue can affect blood biomarker levels, including inflammatory markers [26] and oxidative stress [27]. Evidence from randomized controlled trials (RCTs) has indicated an effect of physical activity in patients with cancer on the levels of circulating growth factors and cytokines (eg, interleukin 6 and tumor necrosis factor alpha) [28,29] and suggests that physical activity might markedly alter the frequency and functional competence of immune cell subsets of the innate immune system (eg, neutrophils, monocytes, and natural killer cells) [30,31]. Concerning the oxidative stress, an excessive accumulation of oxidative stress in cells has been shown to induce marked cellular and molecular damages and likely plays an important role in carcinogenesis, tumor promotion, and breast cancer recurrence and metastasis [32-34]. Moreover, plasma antioxidant defenses seem to be lower in women with breast cancer [34]. On the contrary, physical activity programs have shown to decrease the oxidative stress in patients with chronic diseases other than cancer, in particular through the improvement of enzymatic antioxidant defenses [27,35].

The Advanced stage Breast cancer and Lifestyle Exercise (ABLE) Trial was designed to address the gaps in the current literature. The primary aim is to determine the feasibility of an unsupervised and personalized physical activity intervention in patients with metastatic breast cancer. The secondary aims are to investigate (1) how the physical activity intervention changes the total global physical activity, sedentary time, and physical fitness; (2) how the physical activity intervention changes patient-reported outcomes, including the quality of life and fatigue; (3) how the physical activity intervention changes patients’ anthropometric measurements and body composition; (4) the barriers and facilitators of the adherence to a physical activity program; and (5) whether the physical activity intervention affects the oxidative stress and inflammation as biomarkers of the tumor progression.

## Methods

### Study Design

The ABLE Trial is a single-arm trial that is being conducted in the Léon Bérard Comprehensive Cancer Center (Lyon, France). The study protocol was approved by the French ethics committee (*Comité de protection des personnes Sud-Est IV*), and the study database was reported to the National Commission for Data Protection and Liberties (CNIL; reference number: 1994192). The study is registered on ClinicalTrials.gov (NCT number: NCT03148886).

### Study Population

The inclusion criteria for this study are as follows: (1) female; (2) aged 18-78 years; (3) newly diagnosed with primary or secondary metastatic breast cancer histologically confirmed (ie, within the last 3 months) and treated in a cancer center by chemotherapy or radiotherapy or hormonal therapy or targeted therapy; (4) Eastern Cooperative Oncology Group Performance status <2; (5) able to speak and understand French and able to complete questionnaires and follow instructions in French; and (6) valid health insurance affiliation. For patients willing to participate in the study, confirmation from their treating oncologist of no contraindications to physical activity is required.

The exclusion criteria for this study are as follows: untreated brain metastases; pregnancy; and contraindications to physical activity (eg, uncontrolled hypertension, cardiac disease). All patients must sign an informed consent form.

### Recruitment

Women are screened weekly during the center’s multidisciplinary metastatic breast cancer board meetings, as seen in Figure 1. After checking the inclusion and exclusion criteria, the study is directly proposed by an oncologist or radiotherapist to patients treated by chemotherapy or radiotherapy. As patients treated by hormonal therapy do not come to the center, they receive an information letter and study brochure through post and are contacted by telephone 1 week later to know whether they intend to participate. For all enrolled patients, a physician provides a certificate indicating no contraindications to physical activity, and an appointment is subsequently planned to sign an informed consent and proceed to the baseline evaluation (day one, D1).

### Intervention

#### Adapted Physical Activity Program

The evaluated intervention is a home-based, personalized physical activity program. The frequency, duration, and intensity of physical activity sessions are modulated depending on patients’ capacities.

**Figure 1 figure1:**
[figure not shown]
Participant flow chart for the Advanced stage Breast cancer Lifestyle and Exercise study, Lyon, France (PA: Physical activity).

Patients are encouraged to accumulate at least 150 minutes per week of moderate-to-vigorous intensity physical activity to maintain and improve health benefits. In addition, patients are asked to walk at least 30 minutes per day, increase their activities in their daily routine, and reduce their sedentary time. Several individual strategies are established with patients to attain their objectives (eg, using stairs whenever possible and walking for groceries or shopping). Moreover, meetings at the center with physical activity instructors are proposed depending on patients’ needs. Patients receive feedback at least monthly from their instructor. For patients undergoing chemotherapy, meetings take place during their day care visits at the cancer center. For patients with hormonal therapy treatment, meetings occur by phone or during a consultation with a physician in the center.

